### Primary and secondary outcomes

Progression of kidney disease will be assessed according to glomerular filtration rate measurements, estimated from the four variables formula for Modification of Diet in Renal Disease (MDRD). The glomerular filtration rate will be estimated in the intervention and control groups from serum creatinine measurements obtained at the baseline, in the 8^th^ and 16^th^ weeks after the start of the intervention and in the 8^th^ week after the end of the intervention. Protein excretion in urine will be evaluated through the proteinuria ratio in milligrams per deciliter (mg/dl) and the creatininuria ratio (mg/dl), taking the index to be normal when it is less than 0.3. A secondary outcome is quality of life, which will be measured using the Medical Outcomes Study Short Form 36 item (SF-36). It comprises eight scales, each scored from 0 to 100.

### Measurements

Blood pressure: for measurements of systolic and diastolic blood pressure, the mean from two measurements made five minutes apart, with the patient seated, will be used. In order to maintain precision, an automatic device for blood pressure measurement will be used (Omron HEM-705-CP), and the adult cuff size will be selected (the cuff width should be 40% of the brachial circumference and its length should be 80%). The patients will remain seated, with the arm supported at heart level. They will remain at rest for five minutes before the measurement and should not have had coffee or smoked within the preceding 30 minutes.

Medications: to measure the consumption of medications, the questionnaire standardized by Bertoldi and colleagues [24] will be used. The numbers and names of medications used by the participants will be recorded.

Blood and urine samples: will be collected after the participants have been under fasting conditions for 12 hours. Assays to determine serum levels of total cholesterol, HDL cholesterol, triglycerides, blood glucose, ultrasensitive C-reactive protein, hemoglobin and hematocrit will be performed. Protein and creatinine concentrations will be measured in urine samples. Proteinuria will be assayed using the colorimetric method, with pyrogallol red in a photometric device. Plasma and urinary creatinine will be analyzed by means of kinetics, Jaffe’s method with distilled water and using Roche reagent. Total cholesterol and HDL cholesterol will be measured by means of a colorimetric cholesterol esterase enzymatic method.

Ankle-arm index: this index will be measured with the patient in dorsal decubitus, as the mean of two systolic pressure measurements on the dominant brachial artery (right arm for right-handed individuals and left arm for left-handed individuals), to obtain the proximal pressure; and on the posterior tibial of the ipsilateral leg to obtain the distal pressure [25]. These measurements will be made, respectively, by means of a sphygmomanometer and the Microem DV10 portable vascular Doppler ultrasound equipment (ANVISA/MS registration no. 10301810012). The index is then obtained as the ratio between the distal and proximal pressures.

In addition to these variables, physical activity before and after the intervention will be quantified. Physical activity practice during leisure time and as a means of transport will be evaluated using the long version of the International Physical Activity Questionnaire (IPAQ) [26]. This outcome will assess the sustainability of the intervention in the intervention group, eight weeks after the end of the programmed exercise sessions, in comparison with the level of physical activity in the control group at the same point in time.

### Co-variables

At the baseline, in addition to data on sociodemographic, behavioral and anthropometric characteristics, length of time with the diagnosis of hypertension and laboratory parameters, information on the following factors will be gathered:

1. Medications:

a) Use of antihypertensive agents that block the angiotensin system (angiotensin-converting enzyme inhibitors and angiotensin receptor blockers) that may be associated with diminished progression of kidney disease;

b) Use of non-steroidal anti-inflammatory drugs, which, on the contrary, may increase the progression of chronic kidney disease.

c) Level of physical activity before the start of the study.

### Quality control

The day-to-day progress of the study will be closely monitored by the coordinator, who will be available to resolve any queries that may arise over the course of the fieldwork. The physical exercise sessions of the intervention group will be monitored by a research assistant, who will record the names of those who are present, identify those who are absent and organize home visits within the next 24 hours after the session for the participants who did not attend. According to the reason for the absence, appropriate measures will be taken in order to ensure maximum adherence to the study among the participants.

### Data colleting and analysis

Data will be double-entered into the Epi-Info software in order to make subsequent comparison and thus ensure greater data quality. Automatic data checking will be performed, at the time of data entry, using the check function of Epi-Info, in order to verify range and consistency. To identify and correct inconsistencies of coding, revision and data entry, data cleaning will be performed by obtaining the frequencies of the variables gathered, using the Stata 11.0 software. This software will also be used for the data analysis. A two-tailed significance level of 5 % will be used for all the analyses. The two groups will firstly be compared in terms of the frequencies of the independent variables (demographic, socioeconomic and behavioral factors and time since arterial hypertension was diagnosed), blood pressure levels, glomerular filtration rates and other dependent variables. All analyses will be conducted using intention to treat, i.e., each individual will be analyzed in the group to which he or she was initially allocated, independent of dropouts from the intervention group or any beginning of physical activity among members of the control group. Outcome variables (glomerular filtration rate and quality of life) will be compared in the two groups using *T*-test. We will use confidence intervals for estimating treatment effects.

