**Methods:**

The participants will be located through screening hypertensive patients attended within the public healthcare network in Pelotas, a city in south of Brazil. Eligible individuals will be those with glomerular filtration rate between 15 and 59 ml/min x 1.73 m^2^. The randomization will be done in fixed-size blocks of six individuals such that 75 participants will be allocated to each group. At baseline, information on demographic, socioeconomic, behavioral, anthropometric, blood pressure and quality-of-life variables will be collected, and laboratory tests will be performed. The intervention will consist of three weekly physical exercise sessions lasting 60–75 minutes each, with a total duration of 16 weeks. The outcomes will be the kidney function progression rate, quality of life, blood pressure, lipid profile, hemoglobin level, ultrasensitive C-reactive protein level, and ankle-arm index. The patients in both groups (intervention and control) will be reassessed and compared partway through the study (8^th^ week), at the end of the intervention (16^th^ week) and in the 8^th^ week after the end of the intervention.

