### Sample size calculation

Due to the lack of baseline population-based Brazilian data on kidney function, we carried out a pilot study in a subsample of hypertensive patients registered in eight primary health care units in the city of Pelotas in 2010 in order to obtain the estimates needed for the sample size calculation. Through reviewing 3800 medical files, 290 patients with glomerular filtration rates of less than 60 ml/min x 1.73 m^2^ were identified. In this subsample, the glomerular filtration rate of non-diabetic hypertensive patients in stages 3 and 4 of chronic kidney disease was 48.47 ± 9.61 ml/min x 1.73 m^2^. To identify a post-intervention difference greater than or equal to 10% between the intervention and control groups that is significant at the 5% level (two-tailed), with a power of 80% at the end of 16 weeks, it will be necessary to include 63 patients in each group of the study. We decided to expand the sample to 75 patients per group in order to take follow-up losses into account based on previous trials with chronic kidney disease patients. This sample size also allows detecting baseline vs. post-intervention differences of 10% or greater in both groups.

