### Follow-up and adherence to the study

Since the aim of the study is to assess the efficacy of the intervention, strategies for ensuring follow-ups with complete adherence will be used. At the start of the study, the participants will be informed about the importance of the follow-up, and the names, addresses and telephone numbers of two individuals who are close to the participant and who might be able to inform where the participant can be found will be recorded. Over the course of the study, the participants in the intervention group will be contacted by telephone on the day preceding the physical activity sessions. Participants will be offered a snack at the end of each intervention session, transportation vouchers for them to come to the sessions and a pair of training shoes and sports clothes to use at the physical exercise sessions. Participants who do not come to one of the sessions will be sought in their homes to find out why they had been absent. If necessary to ensure adherence, the study will provide door-to-door transportation, free of charge for participants. The intervention will take place between August 2011 and July 2012. The sessions will be administered by physical education professionals, through an agreement with the School of Physical Education of the Federal University of Pelotas, within the premises of the school.

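### The planned t-test makes the week-16 comparison an observed-case one unless values are imputed; a longitudinal mixed model on data already collected would serve the intention-to-treat aim better

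*Protocol article*

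**What the plan says.** **Analysis population and method.** In the protocol article, Data colleting and analysis, all analyses are by intention to treat, defined as analysis in the allocated group "independent of dropouts from the intervention group or any beginning of physical activity among members of the control group". GFR and quality of life are then compared between the two groups by t-test, with confidence intervals for the treatment effect. No other method for the treatment comparison is named. The section ties the test to no visit and mentions neither covariates nor missing outcomes.

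**Allowance for losses.** Sample size calculation sets the target at 16 weeks, finds that "it will be necessary to include 63 patients in each group of the study", and continues: "We decided to expand the sample to 75 patients per group in order to take follow-up losses into account". No loss rate is given.

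**Data collected.** Primary and secondary outcomes plans GFR at baseline, week 8, week 16 and 8 weeks after the intervention ends (week 24). Random allocation places the follow-up visits in participants' homes. The abstract says the arms are compared at each of the three follow-up visits.

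**Retention.** Follow-up and adherence to the study provides tracing contacts for participants in general. For the exercise sessions, "the participants in the intervention group will be contacted by telephone on the day preceding the physical activity sessions", and a missed session prompts a home visit.

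**The concern.** A two-sample t-test can use only people who have a value at the visit being compared. The enrolment margin over 63 makes sense only if some participants are expected to contribute nothing to that comparison. So the plan promises to analyse individuals as allocated, expects to lose some, and names a method that cannot by itself include them.

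Two things are at stake:

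- **Bias.** If the arms differ in how many people are lost, or in how the lost differ from those observed, the week-16 difference is shifted. The arms carry different burdens (three sessions a week for 16 weeks against usual care) and get different amounts of contact, so equal and comparable loss cannot be taken for granted. The direction of any shift is unknown.
- **Information.** A person missing at week 16 may still have GFR at baseline, week 8 or week 24, and nearly everyone observed at week 16 will have a baseline value. An unadjusted t-test uses none of this for the week-16 contrast.

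**Working it through.** **Inputs, all from Sample size calculation unless noted**

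- Error rates and time point: "significant at the 5% level (two-tailed), with a power of 80% at the end of 16 weeks".
- GFR mean and SD: "in stages 3 and 4 of chronic kidney disease was 48.47 ± 9.61" ml/min x 1.73 m².
- Target: "post-intervention difference greater than or equal to 10% between the intervention and control groups".
- Needed per group: 63. Enrolled per group: 75, equal allocation (abstract: "75 participants will be allocated to each group").

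**1. Reproduce the plan's figure.** Target difference = 0.10 × 48.47 = 4.847 ml/min. Standardised difference = 4.847 / 9.61 = 0.504. The normal approximation, n = 2(1.96 + 0.842)² / 0.504², gives 62 per group. The noncentral t calculation gives 62.7, that is 63. The stated 63 is reproduced.

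**2. Implied loss.** 1 − 63/75 = 12/75 = 16%; equivalently 63/0.84 = 75. This is derived: the article states no rate, and it is an allowance rather than a forecast.

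**3. Power.** By the noncentral t, power is 80.2% with 63 analysed per arm and 86.6% with 75. Losses within the allowance do not take power below the stated 80%.

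**4. Bias of the observed-case difference.** Let p be the proportion missing in an arm and g the mean of the observed minus the mean of the missing. The full mean is (1 − p) × observed + p × missing, so the observed mean exceeds the full mean by p × g. Hence

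bias = p(intervention) × g(intervention) − p(control) × g(control).

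The article gives no information on g, so the values below are assumptions.

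| Loss, intervention / control | Gap assumed (ml/min) | Bias (ml/min) | Share of 4.847 |
|---|---|---|---|
| 16% / 16% | any, equal in both arms | 0 | 0% |
| 16% / 16% | 0 in both arms | 0 | 0% |
| 16% / 16% | 5, intervention only | 0.16 × 5 = 0.8 | 17% |
| 16% / 16% | 10, intervention only | 0.16 × 10 = 1.6 | 33% |
| 24% / 8% | 4.847, equal in both arms | (0.24 − 0.08) × 4.847 = 0.78 | 16% |
| 24% / 8% | 9.61, equal in both arms | (0.24 − 0.08) × 9.61 = 1.54 | 32% |

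A positive sign flatters exercise (the intervention patients lost had lower GFR). The same gap in the control arm alone reverses the sign.

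**5. Scale.** With 63 per arm the standard error is 9.61 × √(2/63) = 1.71 ml/min. Biases of 0.78 and 1.54 would raise the two-sided 5% error rate to about 7.4% and 14.6%. For bias to equal the whole target at 16% loss, the gap in one arm would have to be 4.847 / 0.16 = 30.3 ml/min, more than three SDs.

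**6. Precision.** Adjusting for baseline multiplies the variance of the week-16 contrast by roughly 1 − r², where r is the correlation between baseline and week-16 GFR. The article gives no r, so I put no figure on the gain.

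**The case against.** The strongest reply is that handling of missing outcomes is commonly left to the full protocol or analysis plan, neither of which is shown, so the article's silence is not a fault. That is right, and silence is not the point made here. The article does name its estimator, and a better one exists for the data it collects.

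Several stronger readings are tempting, and the documents do not support them:

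- *That the plan excludes everyone without a week-16 value, against its own intention-to-treat promise.* No exclusion rule is written, and imputation before a t-test is not ruled out. The quoted clause concerns leaving the programme and controls taking up exercise. A t-test by allocated group is compatible with it.
- *That this is a completer analysis.* Exercise takes place at the university school and outcomes are measured at home, so stopping exercise need not mean losing the outcome.
- *That the other GFR values go unused.* Baseline, week 8 and week 24 are compared in their own right. They only fail to inform the week-16 contrast.
- *That the t-test is unbiased only if losses are completely at random.* Health-related loss that is equal in both arms, with equal gaps, gives zero bias.
- *That follow-up effort favours one arm.* The calls and absence visits concern sessions that controls do not have, and tracing contacts are not limited by arm. Extra contact might even improve retention in the intervention arm.

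It also stands that the bias figures are assumed scenarios and that power is intact.

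**Conclusion.** The point holds as a worthwhile, inexpensive improvement, not as an error or a contradiction in the plan. As written, and unless values are imputed, the week-16 comparison is an observed-case one, unadjusted for baseline, that takes nothing from the other visits of participants missing at week 16. The possible bias is 0 to 1.6 ml/min (0 to 33% of the 4.85 target), assuming 16% loss and a gap of 0 to 10 ml/min confined to one arm. It is zero if loss and gaps are the same in both arms. The 16% rests on reading the step from 63 to 75 as the expected loss. Confidence is medium, because the documents give neither actual loss rates nor any gap between observed and missing patients, and the analysis plan is not shown.

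**What to change.** - Replace the t-test for GFR by one longitudinal mixed model on all randomised participants, using baseline, week 8, week 16 and 8 weeks after the intervention. Fit a common baseline mean, arm-by-visit effects and an unstructured covariance. Take the week-16 contrast, with its confidence interval, as primary.
- Do the same for quality of life, on the visits at which the SF-36 is collected.
- Add one sensitivity analysis that shifts missing week-16 values by a range of fixed amounts (delta adjustment) and shows how far the conclusion holds.
- State that home assessments continue for participants who stop exercising. The article implies this already.

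The cost is a little more analysis work, feasible in the planned Stata software, with no new data and no change in sample size. The model relies on outcomes being missing at random given the observed values; the delta adjustment tests that assumption. If the unseen analysis plan already specifies an analysis of this kind, confirming it is enough.

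### GFR and quality of life are compared by a t-test with no stated baseline adjustment; the test is valid, but adjusting for baseline would add precision at no cost

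*Protocol article*

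**What the plan says.** In the protocol article, the section on data collection and analysis names the method outright: "Outcome variables (glomerular filtration rate and quality of life) will be compared in the two groups using" a t-test, with confidence intervals for the treatment effects. It mentions no covariate, change score or longitudinal model, and does not say which visit is tested. It compares the groups on GFR and other variables first, but gives that comparison no part in the outcome analysis. The section on co-variables likewise states no role for them there.

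The sample size section indicates which t-test is meant: "To identify a post-intervention difference greater than or equal to 10% between the intervention and control groups", "with a power of 80% at the end of 16 weeks". Its variance input is the spread of GFR across pilot patients at one time: "chronic kidney disease was 48.47 ± 9.61 ml/min x 1.73 m^2".

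The baseline values will exist. The outcomes section estimates GFR "from serum creatinine measurements obtained at the baseline", at weeks 8 and 16, and 8 weeks after the intervention ends. The section on random allocation lists quality of life among the baseline data.

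The abstract words the outcome differently: "The outcomes will be the kidney function progression rate, quality of life, blood pressure" and others. Neither the sample size section nor the analysis section defines a rate or a change.

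**The concern.** A patient's GFR before the programme is likely to predict the GFR 16 weeks later. A two-group t-test of week-16 values treats all between-patient variation as noise, including the part that baseline GFR explains. A chance difference between the groups at baseline also passes into the estimated effect in proportion to the correlation. Allocation is in blocks of six with no stratification by GFR stated, so the design does not limit such a difference. The same applies to each SF-36 scale.

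At stake are a wider confidence interval than necessary and less power for effects below the design target. There is also a loosely fixed primary estimate. The aim and abstract speak of deterioration and progression, the sample size speaks of a post-intervention difference, and the analysis section does not say which is tested. That leaves room to choose between post values, change and an adjusted analysis once the data are known.

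**Working it through.** **Inputs from the protocol article.** Pilot mean GFR 48.47 and SD 9.61 ml/min x 1.73 m²; target difference 10%; two-sided 5% level; 80% power at week 16; 63 per group, expanded to 75 (sample size section); 1:1 allocation (abstract).

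**Assumption.** The correlation r between baseline and week-16 GFR is not given, so a range of 0.3 to 0.9 is shown. The SD is taken as 9.61 at both times.

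**1. The plan's own figure.** Target = 0.10 × 48.47 = 4.847. Standardised difference = 4.847 / 9.61 = 0.504. The normal approximation, n = 2 × [9.61 × (1.96 + 0.84) / 4.847]², gives 61.7, so 62 per group. The exact two-sample t calculation gives power of 79.6% at 62 and 80.2% at 63. The stated 63 is therefore the sample size for an unadjusted t-test of a single post-intervention value. With all 75 per group followed, power is 86.6%.

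**2. Detectable difference at 63 per group, 80% power.** Unadjusted (exact t): 4.83 ml/min. ANCOVA has residual SD 9.61 × √(1 − r²), so the detectable difference is about 4.83 × √(1 − r²). The equivalent gain in sample size is 1/(1 − r²).

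| r (assumed) | Residual SD | Detectable difference, ANCOVA | Variance removed (r²) | Equivalent sample |
|---|---|---|---|---|
| 0.3 | 9.17 | 4.61 | 9% | 1.1 times |
| 0.5 | 8.32 | 4.19 | 25% | 1.3 times |
| 0.7 | 6.86 | 3.45 | 49% | 2.0 times |
| 0.8 | 5.77 | 2.90 | 64% | 2.8 times |
| 0.9 | 4.19 | 2.11 | 81% | 5.3 times |

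**3. Chance baseline imbalance.** SE of the baseline difference = 9.61 × √(2/75) = 1.57 ml/min, or 9.61 × √(2/63) = 1.71 at 63 per group. A one-SE imbalance at 75 per group is 1.57 / 4.847 = 32% of the target. The unadjusted estimate carries r times the imbalance, for example 0.7 × 1.57 = 1.10 ml/min at r = 0.7.

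**4. If the t-test is on change from baseline.** The change score has variance 2 × 9.61² × (1 − r), and ANCOVA has 9.61² × (1 − r²). The ratio of ANCOVA to change score is (1 + r)/2: 0.65, 0.75, 0.85, 0.90 and 0.95 at r = 0.3, 0.5, 0.7, 0.8 and 0.9. ANCOVA then lowers the variance by 15% to 5% for r from 0.7 to 0.9, and by 25% to 35% for r from 0.5 down to 0.3. Below r = 0.5 the change-score test is less precise than the post-value test. At r = 0.3 it needs 1.4 × 61.7 = 86.4, so 87 per group, against 62 by the same normal approximation.

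**5. Quality of life.** The article gives no SD or correlation for the SF-36 scales, so the gain there cannot be sized.

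**The case against.** The strongest reply is that design and analysis agree. The sample size is for a t-test, the analysis is a t-test, the type I error is controlled and the stated power is met. Chance imbalance is not bias, since the unadjusted confidence interval already allows for it. All of this stands, and it limits the point to efficiency and to how firmly the estimate is fixed.

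The post-value reading is also an inference. The analysis section does not exclude a t-test on change, and the wording about progression would fit one. This stands too, although the reproduced 63 per group favours post values. Under the change reading the gain is that of step 4, not that of the table.

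Two stronger readings are tempting, and the article supports neither:

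- **That a post-value test does not estimate progression.** Under randomisation the difference in week-16 means has the same expectation as the difference in mean change, so it estimates the effect on 16-week change without bias. ANCOVA targets the same quantity. Neither yields a rate.
- **That the trial gives up most of its precision.** In variance terms this needs r above about 0.71, and halving the standard error needs r above about 0.87. The article gives no r. The restricted eligibility range (GFR 15 to 59) and error in creatinine-based estimates would both lower it.

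The article condenses a fuller plan, but here it states a method, so this is not a detail left to a document that is not shown.

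**Conclusion.** The point holds as an available improvement. The stated comparison uses no baseline adjustment, and the sample size implies a test of week-16 GFR values. The t-test is valid and unbiased, and it has about 80% power for 4.85 ml/min with 63 per group.

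Against a post-value test, baseline adjustment would reduce the detectable difference from about 4.83 to between 4.6 and 2.1 ml/min as r goes from 0.3 to 0.9. It would also correct for chance baseline imbalance. Against a change-score test the variance falls by 5% to 15% for r from 0.7 to 0.9. The size therefore rests on an unstated correlation and an unstated choice of response; the direction does not, for any r above 0 and short of 1. This should be fixed, but leaving it would not invalidate the trial.

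**What to change.** State in the analysis section that the primary estimate is the between-group difference in week-16 eGFR adjusted for baseline eGFR by ANCOVA, with its 95% confidence interval. Using change as the response in the same model gives the same treatment estimate, so this also settles the choice between post value and change. Analyse each SF-36 scale with its own baseline score as covariate, and keep the t-test as a sensitivity analysis. Reword the abstract's outcome to match, because this estimate is a difference at 16 weeks and not a rate. If the full analysis plan already specifies this, only the article needs aligning.

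The cost is a sentence or two in the analysis section and one phrase in the abstract. It needs no new data, visits or patients, and the sample size can stay. The change should be recorded before outcomes are compared by group.
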